**Number of partners in past year and lifetime**

We will ask men to report their overall number of lifetime sexual partners and number of partners they have had in the past year. Several studies have shown that young men with more lifetime partners are more likely to have perpetrated violence towards their sexual partners.([Dunkle et al., 2004](#_ENREF_21); [Harrison, O'Sullivan, Hoffman, Dolezal, & Morrell, 2006](#_ENREF_29); [Maman et al., 2010](#_ENREF_51)) Thus, we will include lifetime number of partners as a mediating variable in our violence analysis. In addition, we will analyze men’s number of lifetime partners as an outcome, indicating risk of HIV transmission to women.

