## 1.7 Rationale for Working with Camps

**Through an NIMH intervention development grant (R21 MH080577) our group identified viable locations and feasible strategies for intervening with high risk networks of men.** Using the PLACE methodology we identified and characterized 73 venues, locally named “camps,” where young men socialize within one ward of Dar es Salaam. While some health risk behaviors occur among camp members, camps are primarily constituted by entrepreneurial youth who use them as meeting spaces to provide one another with social support. Camps we surveyed had existed for an average of 8 years (range 4-13 years), had an average of 52 members between the ages of 15-40 years, and were formed by men who wanted to claim a space where they could engage in social activities such as soccer or playing pool. The 670 men in camps whom we interviewed reported substantial risk behaviors: 47% reported 2 or more sex partners in the past year; 47% of those who had ever had sex reported one or more concurrent sexual partnerships in the past six months; 21% had at least one symptom of an STI in the past 4 weeks; and 41% reported ever perpetrating physical or sexual violence against a female partner. The majority of men (73%) socialized in their camp daily for several hours, and over half (53%) were unemployed. Our qualitative research described how youth developed a democratic system for running the camps that minimally included a chairperson, a secretary and a treasurer.([Yamanis et al., 2010](#_ENREF_100)) Members paid dues to belong, and all camps maintained written membership records. In the second year of the grant, which was recently completed in August, 2011, we partnered with a microfinance organization to pilot a microfinance and health leadership intervention with men in three camps. Nineteen men received a two-week business training course, received loans of $100 each, participated in groups to guarantee loan repayment, and had weekly repayment sessions over 6 months. We also recruited 30 peer-nominated leaders from the three camps to participate in health leadership training that emphasized communication skills and strategies to influence peer behavior. Results of the pilot demonstrate the feasibility and acceptability of this multi-level approach. Only one of the 19 men who received a loan defaulted on his loan. We learned important strategies to motivate and support men through the repayment process, such as having more frequent repayment sessions, building ongoing business skill training into the regular repayment sessions, and providing more explicit instructions on record keeping. The twenty leaders who completed the initial two week training course on communication and social influence remained engaged in the pilot intervention for 9 months. Two additional booster training sessions, and maintenance of regular records of their communications with their peers about HIV and violence prevention were also part of the intervention.

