### 4.3.1 Participant Eligibility Criteria

Study participants will be male members of camps in Dar es Salaam, Tanzania. Camps are predominately male social groups where members meet in fixed locations. Eligibility criteria for camp members to be able to participate in the study include:

- Participant is at least 15 years old
- Has been member of camp for at least 3 months
- Visits camp at least once a week
- Intends to live in Dar es Salaam for next 30 months
- Willing to give contact information of self and relative or friend

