## 7.4 Secondary Outcomes - Behavioral Outcomes

All secondary outcomes except for microfinance outcomes will be measured at baseline, 12 months and 30 months. Microfinance outcomes will be measured at 12 and 30 months only.

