***Interviewer:***

→ Now I would like to ask some more personal questions about you and your relationships. Please remember that your answers will be confidential.

| **No.** | **Questions and Filters** | **Coding Categories** | **Codes** | **Skip to:** | **VARIABLE** |
| --- | --- | --- | --- | --- | --- |
| Q1401 | Have you ever had sex?  • Vaginal sex is when a man puts his penis in the vagina of a woman; [some people call this [Swahili term].  • Anal sex is when a man puts his penis in the rectum of a man or a woman; [some people call this [Swahili term]. | NO  YES | 0  1 | **Q1409 and then AND SKIP to SECTION 16** | SEX_EVR |
| Q1402 | How old were you when you had sex for the first time? If you can’t recall the exact age, please give a best estimate. | __ __ YEARS  DON’T KNOW | 88 |  | SEX_AGE |
| Q1403 | How would you describe the first time that you had sex? Would you say that you wanted to have sex, you did not want to have sex but it happened anyway, or were you forced to have sex? | WANTED TO HAVE SEX  DID NOT WANT TO HAVE SEX BUT HAPPENED ANYWAY  WAS FORCED TO HAVE SEX | 1  2  3 |  | SEX_1DES |
| Q1404 | Did you experience any of the following types of situations the first time you had sex?  VERBAL THREATS  PHYSICAL THREATS  PHYSICAL FORCE/HOLDING DOWN  BEATING  HUMILIATING OR DEGRADING SEX ACTS | NO  YES | 0  1 |  | SEX1_VER  SEX1_PHY  SEX1_FRC  SEX1_DEG |
| Q1405 | In total, how many people have you ever had sex with in your lifetime? | __ __ # PERSONS |  | *Note that if this value is less than 3, the participant will only be asked about the corresponding # of partners in the Sexual Network Section | SEXE_NUM |
| Q1406 | In total, how many people have you had sex with in the past 12 months?  This includes people you had sex with only once and people you have had sex with regularly, such as a spouse or someone you live with.  If you can’t recall the exact number, please give a best guess. | NONE  __ __ # PERSONS | 0 |  | SXP12_NUM |
| Q1407 | How many of these partners were women and how many were men? | WOMEN___________  MEN___________ |  | **ASK ONLY IF Q100 = 1**  ***This should total Q1406** | MSM_NUM |
| Q1408 | In general, how would you consider your chances of getting HIV/AIDS? Are they small, moderate, great, or no risk at all? | NO RISK AT ALL  SMALL  MODERATE  GREAT | 1  2  3  4 |  | HIVRISK |
| Q1409 | Have you ever had a test for HIV/AIDS? | NO  YES  DON’T KNOW | 0  1  88 | **Q1501 (UNLESS Q1401 =0)** | TESTHIV |

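### Lifetime number of partners is used as a mediator of the violence effect and as an outcome without separating out the partners gained before baseline, which the intervention cannot affect

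*Protocol*

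**What the plan says.** Section 7.4.1 of the protocol, under the item on number of partners, collects both the past-year and the lifetime count. It cites studies in which young men with more lifetime partners were more likely to have been violent, and concludes from this that "we will include lifetime number of partners as a mediating variable in our violence analysis". It then adds that the team will analyse "number of lifetime partners as an outcome, indicating risk of HIV transmission to women".

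The survey in Appendix D, Section 14, has one item for each count. Q1405 asks "In total, how many people have you ever had sex with in your lifetime"; Q1406 asks "In total, how many people have you had sex with in the past 12 months". Section 7.4 sets the schedule: "All secondary outcomes except for microfinance outcomes will be measured at baseline, 12 months and 30 months".

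Section 9.1.3 compares arms at 12 and 30 months and leaves covariates to be added as needed, without naming any. The mediation analysis in section 9.1.4 runs only if program effects are found. Lifetime partners is not named in the mediator lists of the Protocol Summary, section 2.3, section 3.3 or section 9.1.4; the last has only a broad domain on sexual relationships and risk that could contain it.

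**The concern.** A mediator has to be something the intervention changes, and that in turn changes the outcome. A true lifetime count can only stay level or rise between waves, and at every wave it carries all partners acquired before the trial. Those partners are a pre-treatment characteristic. The reason given in section 7.4.1, that men with more partners are more often violent, is an association. It describes a baseline risk factor and does not show that the intervention acts through partner number.

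Two things are at stake. In the mediation analysis, differences between men in lifetime count partly reflect their history, so the estimated link from partner number to violence takes in whatever drove both before the trial. In the outcome analysis, the partners already counted at baseline dilute the relative difference between arms and add variance.

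**Working it through.** The protocol states no figure for lifetime partners, so there is none to reproduce. The size has to be shown on assumed inputs.

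**Inputs from the protocol.** Assessments at baseline, 12 and 30 months, so at most 2.5 years of accrual after baseline (section 7.4). Minimum age: "Participant is at least 15 years old", with no upper limit (section 4.3.1). In the earlier survey, camps "had an average of 52 members between the ages of 15-40 years" and "47% reported 2 or more sex partners in the past year" (section 1.7). Section 9.1.1 plans for 36.2 sexually active men among 52 per camp, 36.2 / 52 = 69.6%.

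**Assumed inputs.** Lifetime partners at baseline L0 = 4, 6 or 10; new partners per year r = 1.5 or 2.5; a true 25% cut in new partners over the whole 2.5 years.

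**Formulas.** Without the intervention effect, the month-30 count is L0 + 2.5r. The share fixed before baseline is L0 / (L0 + 2.5r). The apparent cut in the lifetime count is 0.25 × 2.5r / (L0 + 2.5r).

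| L0 | r | Month-30 count | Fixed before baseline | Apparent cut |
| --- | --- | --- | --- | --- |
| 4 | 1.5 | 7.75 | 52% | 12.1% |
| 4 | 2.5 | 10.25 | 39% | 15.2% |
| 6 | 1.5 | 9.75 | 62% | 9.6% |
| 6 | 2.5 | 12.25 | 49% | 12.8% |
| 10 | 1.5 | 13.75 | 73% | 6.8% |
| 10 | 2.5 | 16.25 | 62% | 9.6% |

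**Second route, by length of sexual history.** With a constant rate of new partners and T years of history at baseline, the share fixed is T / (T + 2.5) at month 30 and T / (T + 1) at month 12. A 30% cut after baseline (assumed; section 1.6 quotes that size for network-leader interventions on risk behaviour) gives a month-30 ratio of 1 − 0.30 × 2.5 / (T + 2.5).

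| T (years) | Fixed, month 30 | Fixed, month 12 | Month-30 ratio (true 0.70) |
| --- | --- | --- | --- |
| 0 | 0% | 0% | 0.70 |
| 1 | 29% | 50% | 0.79 |
| 2.5 | 50% | 71% | 0.85 |
| 5 | 67% | 83% | 0.90 |
| 10 | 80% | 91% | 0.94 |

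**Illustrative power at month 30.** Assumptions: 1249 × 0.8 ≈ 1000 men, 500 per arm; gamma-Poisson rates with mean 2 a year and shape 1; a 30% cut; two-sided 0.05; no clustering; 1000 simulated trials per T.

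| T (years) | Raw lifetime count | Past-12-month count | Lifetime count adjusted for baseline |
| --- | --- | --- | --- |
| 1 | 95% | about 99% | about 100% |
| 2.5 | 70% | about 99% | about 100% |
| 5 | 37% | about 99% | about 100% |
| 10 | 18% | about 99% | about 100% |

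Clustering would lower all of these. The past-12-month column treats every partner as new. What matters is the contrast: the loss belongs to the unadjusted lifetime count.

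**Mediation path.** No indirect effect was modelled, so this is reasoning only. Randomisation balances pre-baseline partners in expectation. On the path from arm to mediator they therefore add noise without shifting the expected absolute difference. On the path from mediator to violence they bring in pre-trial confounding, which could inflate the association if past partner number marks a disposition to violence.

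**The case against.** A reader might infer several stronger things. The protocol does not support them.

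- *That most of the count is fixed before baseline.* The protocol gives neither lifetime counts nor length of sexual history. In two of the six assumed combinations the fixed share is below half (39% and 49%). About 30% of camp men are planned as not sexually active, and delay of debut is itself an endpoint; for men with no partners yet, nothing is fixed.
- *That the intervention cannot change the lifetime count.* This is true only of the pre-baseline part. Partners gained over up to 30 months can differ between arms.
- *That the mediated effect is biased toward zero.* The dilution arithmetic concerns an outcome mean. The confounded path to violence could push the indirect effect either way.
- *That the outcome comparison loses most of its sensitivity.* Adjustment for the baseline count, which is collected, restores it. Section 9.1.3 permits covariates, and a separate analysis plan could specify this one.

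It is also fair to say that section 7.4.1 already collects the past-year count, that the secondary endpoint is elsewhere just number of sexual partners, and that the mediator sentence may be loose wording for a covariate. All of this narrows the point. What stands is that the sentence assigns the mediator role expressly, on reasoning that describes a risk factor, and that neither role is limited to partners gained after baseline.

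**Conclusion.** The point holds in this limited form. Partners acquired before baseline cannot carry an intervention effect, so the cumulative count is the wrong mediator as written and a diluted outcome unless adjusted for its baseline value. On the assumed inputs about 39% to 73% of the month-30 count predates baseline, and a 25% cut in new partners appears as about 7% to 15%. These figures rest on assumed partner numbers and a constant effect; the direction of bias in the mediated effect is not established. The consequence is confined to a secondary outcome and to a mediation analysis that is run only if program effects are found. Neither primary endpoint depends on it. The change is nonetheless worth making, because the choice is stated and correcting it needs no new data.

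**What to change.** Amend section 7.4.1 as follows.

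- **Mediator:** replace lifetime partners with a post-baseline measure, either past-12-month partners (Q1406) or partners gained since baseline (the difference in Q1405). Where possible measure it before the violence recall window; for example, the month-12 value precedes the 12-month recall at month 30.
- **Covariate:** enter baseline lifetime partners in the violence analysis only as a covariate.
- **Outcome:** use past-12-month partners, or the lifetime count adjusted for its baseline value.
- **Consistency:** align the section with the mediator lists in the Protocol Summary and sections 2.3, 3.3 and 9.1.4, so that the chosen measure is named in each or in none.

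The cost is wording only, since both items are already in the survey. There is a small trade-off: at month 30 the past-12-month count covers only months 18 to 30, missing most of the two-year intervention period, and it includes continuing partners, so it need not show the full effect on new partners. The baseline-adjusted lifetime count covers the whole follow-up and is a reasonable alternative as the outcome.

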**Sexual debut**

We will ask men to report whether they have ever had vaginal or anal intercourse and the age of first intercourse after they report initiating sexual activity.

**HIV testing**

We will ask men to report at each assessment whether they have ever been tested for HIV, tested within the past 12 months (since last assessment), and whether they received their test results. HIV testing is one of the key HIV prevention strategies that will be promoted by the health leaders. In our previous work, we found that 25% of our population of sexually active youth aged 15-19 had ever been tested for HIV.

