## 3.3 Study Duration and Endpoints

The intervention will be implemented for two years, and the total duration of the trial will be 5 years. **The primary endpoints** are sexually transmitted infections including Neisseria gonorrhea (NG), Trichomonas vaginalis (TV), Chlamydia trachomatis (CT), and perpetration of physical or sexual violence against a sexual partner. A random sample of 50% of participating men will be flagged for an STI test at baseline to assess relative prevalence, and all men will be tested at endline. A test of relative prevalence at baseline will aid in establishing equivalency in the two arms; any lack of equivalency then will be controlled for appropriately at endline. All participants will complete a behavioral assessment at baseline, 12 months and 30 months to assess secondary objectives. **Secondary endpoints** are HIV risk and protective behaviors including: gender equity, alcohol and drug use, sexual relations and risk behavior, uptake of HIV counseling and testing; unprotected sexual intercourse; consistent condom use; delay of sexual debut; number of sexual partners, and sexual concurrency. **Key mediators** are hope, future orientation, social cohesion, collective efficacy, emotional distress, sexual networks, social support and social influence.

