## 6.4 Baseline STI Assessment

Urine and blood specimens for diagnosis of STIs (NG, TV, CT) and HIV will be requested from a sample of half of sexually active men at baseline. Baseline testing is employed to compare base prevalence in the two conditions.

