**Aim 2**

HIV risk, gender-based violence perpetration, and their mediators will be assessed at baseline, 12 and 30 months. STI prevalence assessments will occur at baseline and 30 months. Participants selected to provide a biological specimen must have completed the behavioral assessment to be eligible. Separate written consent will be necessary for the behavioral and biological assessments. Potential participants will be excluded from participation based on an inability to provide informed consent. All consent documents will be stored in locked cabinets. Copies of the informed consent script will be provided to prospective participants to keep.

Research assistants will begin each interview by confirming the eligibility of participants. All eligible participants will then be read the informed consent script in Kiswahili and given the chance to ask questions or clarifications on what they are being asked to do in the study. Participants will acknowledge their consent by initialing the line for behavioral assessment and writing the date and their signature on the form.

Upon completion of the survey, participants selected for the biological assessment will meet with nurses who will administer the biological consent. Nurses will explain the purpose and procedure for blood and urine collection in private. Participants will acknowledge their consent by initialing the line for biological assessment.

Participants not selected for the biological assessment will have the opportunity to receive a symptomatic STI assessment with nurses. Nurses will explain the procedure for symptomatic STI assessment. Participants will acknowledge their consent by initialing the line for symptomatic STI assessment.

Written informed consent will be obtained from each participant in the qualitative sub-studies, prior to their participation. Participants will be provided with a copy of their consent form.

The host site has prior experience in obtaining informed consent for prevention trials within the cultural context. The informed consent procedure for this study has been designed to maximize understanding of potential risks. Consent forms will be translated into Kiswahili and piloted with 50 participants to ensure the script is understandable.

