| Q1410 | How many times have you been tested for HIV/AIDS? | __ __ # TIMES TESTED |  |  | TSTHIV_N |
| Q1411 | Have you had a test for HIV/AIDS in the past 12 months? | NO  YES | 0  1 |  | TEST12M |
| Q1412 | Have you ever received your test results? | NO  YES | 0  1 | **Q1501** | RSLTREC |
| Q1413 | What was the result of your most recent HIV test?  Please remember that everything you say in this interview will be kept in confidence. If you are uncomfortable sharing your result, you may choose to skip this question. | POSITIVE  NEGATIVE  INCONCLUSIVE | 1  2  3 |  | HIVSTAT |
| Q1414 | Who have you shared your HIV/AIDS test results with?  Check all that apply  NO ONE  SPOUSE  BOY/GIRLFRIEND  CASUAL PARTNER  FAMILY (Parents, Children, Siblings, etc.)  RELATIVES (Aunts, Uncles, Cousins, Grandparents, etc.)  FRIEND(S)  HEALTH PROFESSIONAL  OTHER ___________________ | NO  YES | 0  1 |  | HIVDISC  HIVDISC_S |

Section 15. Sexual Network

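### The HIV-testing endpoint does not exclude the trial's own baseline HIV test, so ever-tested at both follow-ups is pulled toward no difference between arms

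*Protocol*

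**What the plan says.** Protocol 3.3 lists "uptake of HIV counseling and testing" among the secondary endpoints, and 7.4.1 says that the health leaders will promote testing. Under 7.4.1 men are asked at each assessment "whether they have ever been tested for HIV, tested within the past 12 months (since last assessment", and also whether they received their results.

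The fielded items are in Appendix D, Section 14. Q1409 asks "Have you ever had a test for HIV/AIDS" and Q1411 asks "Have you had a test for HIV/AIDS in the past 12 months". Neither separates a test done by the study from one obtained elsewhere. Section 8.2.3 says that the same survey form serves baseline, 12 and 30 months.

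The trial also performs HIV tests. In 6.4, urine and blood for the STIs "and HIV will be requested from a sample of half of sexually active men at baseline". Section 3.3 describes the sample differently: "A random sample of 50% of participating men will be flagged for an STI test at baseline". On the order of events, 10.2 (Aim 2) states: "Upon completion of the survey, participants selected for the biological assessment will meet with nurses who will administer the biological consent". Section 6.6 has all consenting men give blood at 30 months.

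**The concern.** The baseline study test comes after the baseline answers and before the 12-month answers. A man who had it can truthfully say at follow-up that he has been tested, whichever arm his camp is in and whether or not anyone encouraged him to test. The trial therefore produces a positive outcome in a share of both arms through its own procedures.

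The result is a rise in reported testing from baseline in both arms and a smaller contrast between them. A null finding on a behaviour that the intervention promotes could then come partly from the measurement procedure.

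There is a second, simpler fault. Section 7.4.1 treats the past 12 months and the time since the last assessment as one window, and they are not the same at every visit.

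**Working it through.** **Which measures count the baseline study test**

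| Measure | Month 12 | Month 30 |
|---|---|---|
| Ever tested (Q1409) | Yes | Yes |
| Since last assessment (wording in 7.4.1 only) | Yes | No: the window opens at the month-12 visit |
| Past 12 months (Q1411) | Depends on visit timing | No |

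The month-12 entry for Q1411 is open because the baseline test lies at the edge of a 12-month window. It lies outside that window if visits are timed from the intervention, as the Protocol Summary words it. If the order in 10.2 also holds at month 30, the 30-month test follows the 30-month interview and is not counted either.

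**Recall windows.** The last two assessments are 30 − 12 = 18 months apart. The two windows in 7.4.1 can coincide at month 12 but not at month 30.

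**Inputs for size.** The plan states no effect size or power for HIV testing, so there is no figure to reproduce. Section 9.1.1 gives 36.2 sexually active men among 52 per camp, and 36.2/52 = 0.696. The only testing rate given is 25% ever tested, from sexually active youth aged 15–19 (7.4.1).

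**Model.** Let p be the proportion who would answer yes without the study test, and f the share of men with a study test that they later report. The observed proportion is q = f + (1 − f)p, so the risk difference is multiplied by (1 − f). Men tested before baseline answer yes to ever-tested in either arm and add nothing to the difference. The same factor therefore applies among men untested at baseline.

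- Half of sexually active men sampled, all men analysed: f = 0.5 × 0.696 = 0.348, so 65% of the difference is kept and 35% lost.
- Half of sexually active men sampled, sexually active men analysed: f = 0.50, so 50% is lost.
- 50% of all participating men sampled (3.3): f = 0.50, so 50% is lost.
- If only 60% consent and report (assumed): f = 0.6 × 0.348 = 0.209 over all men, or 0.6 × 0.50 = 0.30 among sexually active men. The loss is 21% or 30%.

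The 35% assumes the same shift in testing among sexually active and other men. If the intervention moved only the sexually active, the loss over all men would also be 50%.

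**Odds-ratio scale (used in 9.1.3).** All pairs of rates below are assumptions.

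| p, control vs intervention | OR, study test excluded | OR, f = 0.348 | OR, f = 0.50 |
|---|---|---|---|
| 25% vs 35% | 1.62 | 1.30 | 1.25 |
| 25% vs 40% | 2.00 | 1.49 | 1.40 |
| 25% vs 50% | 3.00 | 1.98 | 1.80 |
| 50% vs 65% | 1.86 | 1.64 | 1.57 |

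For 25% vs 40%, the observed proportions become 51.1% vs 60.9% at f = 0.348 and 62.5% vs 70.0% at f = 0.50. Across these rows the log odds ratio keeps 55% to 80% of its size at f = 0.348, and 46% to 73% at f = 0.50.

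**Power, for 25% vs 40%.** Take 1249 × 0.8 / 2 ≈ 500 men per arm and 1249 × 0.8 / 60 = 16.65 men per camp. With the upper behavioural ICC of 0.032 (9.1.1), the design effect is 1 + 15.65 × 0.032 = 1.50. Power is about 99% with the study test excluded, 72% at f = 0.348 and 53% at f = 0.50.

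**The case against.** A reader might infer that the effect on testing uptake is halved throughout, or that the trial cannot answer its aim on testing. The documents support neither. Past-12-month testing at month 30 does not count the baseline test, so one of the two testing measures is clean at the final assessment. At month 12, Q1411 may miss the baseline test, and no fielded item asks about the time since the last assessment. Halving also needs near-full consent and later reporting, together with either an analysis among sexually active men or the sampling in 3.3.

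It can also be said that the dilution acts equally in both arms, cannot by itself create a false positive, and touches one of many secondary endpoints. Specimen collection is logged per participant (6.10, 8.2.3), so an analysis plan could stratify on it. Some questions are added at follow-up (7.4.1, 7.6), so the shown instrument may not be the whole of what is asked later.

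These points limit the size of the problem but do not remove it. Ever-tested is the first measure named in 7.4.1 and is affected at both follow-ups. The protocol itself fixes the item wording and says the form is reused. Among men who had the study test, later analysis cannot tell a study test from an outside one. The survey can draw the distinction easily, since Q012 already asks whether blood and urine were given to study staff.

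**Conclusion.** The point holds for ever-tested at 12 and 30 months and for any since-last-assessment measure at 12 months. The bias is toward no difference and favours neither arm. With full consent and reporting it removes about 35% of the risk difference over all men under 6.4, given equal effects in sexually active and other men. It removes about 50% among sexually active men or under 3.3. Lower consent or reporting reduces the loss, and the loss in the odds ratio depends on uptake rates that the protocol does not give. Past-12-month testing at month 30 does not count the baseline test, and Q1411 at month 12 is undetermined. The mismatch of recall windows at month 30 and the disagreement between 3.3 and 6.4 on who is sampled need no assumptions.

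**What to change.** - At 12 and 30 months, add to Q1409–Q1412 the phrase *not counting any test done by our study*, and say the same in 7.4.1.
- Do not use the unmodified ever-tested item as an effect measure.
- Delete the since-last-assessment gloss in 7.4.1, so that the text matches the 12-month window already in Q1411.
- Reconcile 3.3 and 6.4 on whether the baseline sample is half of all participating men or half of sexually active men.

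This costs one phrase in four items and a few words in the protocol text.

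For waves already collected, analyse the sexually active men not selected for baseline specimens, or stratify by the random selection flag. Restricting to sexually active men matters. Under 6.4 the unselected men as a whole are 30.4% + 34.8% = 65.2% of the sample, and 30.4/65.2 = 47% of them are not sexually active, against 30% overall. They are therefore not a random subset of all men. Within the sexually active they are a random half, provided selection is random as 3.3 says. The cost is precision: after 20% attrition about 1249 × 0.8 × 0.348 ≈ 348 men remain for this one endpoint.
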